### Outcomes and endpoints

Asthma classificationsAt T1, asthma classification is defined by the treating specialist clinician using clinical parameters.For other timepoints (T2 and T3).‘Definite yes’= presence of RAO defined by disappearance of wheeze using WheezeScan after 400 µg of inhaled SABA.‘Definite no’= no wheeze documented.‘Possible’=wheeze without clear response post-SABA or does not fit into the definite ‘yes’ or ‘no’ category.Independent classification by a second specialist after reviewing the data at T3.‘i-Asthma’= resolution of symptoms with treatment using WheezeScan data supported by FeNO >25ppb (if available).^11^‘i-no’= no effect of treatment.‘i-possible’= neither ‘yes’ nor ‘no’.Agreement between clinician and WheezeScan detection of wheeze at T1.PROs (PedsQL,^28^ PC-QoL^29^ (if chronic cough present)).Healthcare resource use and costs (healthcare system and family perspectives).Likert scale question relating to usefulness of WheezeScan at T3.See online supplemental file 1 for further description.

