**Methods and analysis:**

Our multicentre prospective cohort study involves recruiting 102 preschool children suspected of asthma. WheezeScan, a user-friendly digital device, incorporates artificial intelligence to objectively define wheeze and its response to bronchodilators. Over 6 weeks, parents/caregivers use the WheezeScan two times per day and whenever wheezing is suspected. If wheeze is detected, an inhaled short-acting β_2_-agonist is administered and WheezeScan determines if wheeze resolves thereafter.

Our primary endpoint is the proportion of children with a definitive asthma diagnosis, compared with baseline, based on the treating clinician’s assessment using WheezeScan data. Our secondary outcomes are PROs, reflecting generic health-related quality-of-life and cough-specific (if chronic cough present) outcomes and health costs.

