Despite the importance of detecting wheeze, there are high levels of disagreement (>50%) between parental and physician reporting of wheeze.^15^ This may cause underdiagnosis or overdiagnosis of asthma and lead to overuse or underuse of medications, children undergoing unnecessary procedures and high parental anxiety.^16 17^ Crucially, failing to recognise wheeze can delay diagnosis, especially if wheeze is recurrent, as it can defer appropriate treatment, which may lead to ongoing exacerbations, doctor visits, hospitalisations and an increased burden on parents/caregivers. In contrast, early recognition and treatment of asthma improves symptoms and quality of life (QoL).^10^,^12^

While detecting wheeze and its reversibility with SABA is not the sole predictor in the diagnostic journey for asthma in preschool children, it is still a crucial step. Addressing the poor reliability of detecting wheeze in young children^15 18^ is a clear clinical gap. Recently, this gap was highlighted by the European Respiratory Society (ERS) Taskforce statement on preschool wheezing disorders.^5^ Its importance is even greater in settings where reporting of respiratory symptoms is more challenging, such as in disadvantaged First Nations communities^19^ and in settings where there are diverse cultures and languages spoken.^18^

Reliable and objective detection of wheeze using digital technology in clinics during face-to-face visits and at home when applied by parents could lead to improved diagnosis from detecting wheeze that responds to asthma treatments. There are now clinically validated tools that can objectively define wheeze. One such tool is the WheezeScan (figure 1, Omron Healthcare, Japan), which is the world’s first clinically validated device^20^ that uses artificial intelligence to detect and differentiate wheeze from other breath sounds in young children aged 4 months to 7 years.^21^ For our study, we chose WheezeScan as its design is user-friendly, ergonomic, light and portable, allowing parents to have it with them at all times and to remove any uncertainty when breathing distress occurs. In a pilot study from Germany involving 20 children, parents detected wheeze in 22/708 (3.1%) routine two times per day recordings, but WheezeScan indicated wheeze was present in 140/708 (19.8%) of the recordings.^20^

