#### Sample size estimates

Our sample size is 102 children. This is based on conservative estimates of 15% being diagnosed with asthma at T1 and 30% at T3, with a correlation between the paired observations of 25%, which provides power>80% to detect a difference of 15% between the proportions. We will replace children with incomplete data and thus we expect to have complete data from 102 children. We conservatively estimate that 33% of children in our target group (preschool children with recurrent wheeze) have asthma (defined as RAO) and when adequately treated will be two times as likely to have significantly improved PRO above their MCID compared with when not treated due to wheeze misclassification known to be >50% in this age group.^15^

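### One positive-then-negative pair of device readings suffices for 'definite yes', whatever the number of recordings, so part or all of a rise in asthma diagnoses could come from repeated testing

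*Protocol article*

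**What the plan says.** Under Outcomes and endpoints, a child is 'definite yes' at T2 and T3 on "presence of RAO defined by disappearance of wheeze using WheezeScan after" one SABA dose. 'Definite no' requires that no wheeze was documented. Everything else is 'possible'. No number of episodes, separate days or confirmation is required. Potential study limitations adds that resolution of wheeze after SABA is the sole basis for RAO.

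On the amount of recording, the abstract says: "Over 6 weeks, parents/caregivers use the WheezeScan two times per day and whenever wheezing is suspected". The T1 section instructs parents for two weeks. The T2 section states continued use only for the 'definite no' group.

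The primary hypothesis is an increase in definitive asthma diagnoses. The Primary endpoint section counts a definite diagnosis (yes/no) as classified by the treating specialist, and McNemar's test is used. The sample size rests on "conservative estimates of 15% being diagnosed with asthma at T1 and 30% at T3".

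**The concern.** The rule reads as if it described one test, but it is applied to dozens of recordings per child. A child who never wheezes can still meet it through one false positive followed by a correct negative, and the chance of that grows with each recording. Wheeze-free children are the ones for whom continued recording is explicitly stated, because they are 'definite no' at T2.

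Device error is not the only route. In a child with intermittent wheeze, a positive reading followed by a negative one ten minutes later can be fluctuation rather than a response to SABA, and the design has no comparator to separate the two.

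At T1 the label comes from a clinical assessment. At T3 it comes from a rule that accumulates over weeks. A rise in asthma 'yes' could therefore appear without any child being better identified, and families who record more would be more likely to receive the label.

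**Working it through.** **The plan's own figure.** Inputs from Sample size estimates: 15% and 30%, paired correlation 0.25, power above 80%. Two-sided alpha of 0.05 is assumed, as none is stated.

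- Both 'yes': 0.15×0.30 + 0.25×√(0.15×0.85×0.30×0.70) = 0.0859.
- Discordant cells: 0.30 − 0.0859 = 0.2141 and 0.15 − 0.0859 = 0.0641, in total 0.2782.
- n = (1.96√0.2782 + 0.8416√(0.2782 − 0.15²))² / 0.15² = 94.6. With continuity correction, (94.6/4)×(1 + √(1 + 2/(94.6×0.15)))² = 101.2, hence 102.

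The figure of 102 reproduces, and the proportion it is based on is asthma 'yes'.

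**Number of recordings.** 2×14 = 28 routine recordings by T2 and 2×42 = 84 by T3. Recordings made on suspicion are extra.

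**False sequences in a wheeze-free child.** Let f = 1 − specificity. One recording gives a false positive-then-negative pair with probability q = f(1 − f). With independent errors, P(at least one in m) = 1 − (1 − q)^m. P(at least two) subtracts a further mq(1 − q)^(m−1). Specificity is an assumption.

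| Specificity | ≥1, m = 28 | ≥1, m = 84 | ≥2, m = 84 | ≥3, m = 84 |
|---|---|---|---|---|
| 99.9% | 3% | 8% | 0.3% | <0.1% |
| 99.5% | 13% | 34% | 7% | 1% |
| 99% | 24% | 57% | 20% | 5% |
| 98% | 43% | 81% | 49% | 23% |

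To reach 30% with m = 84, q must be 1 − 0.70^(1/84) = 0.42%, a specificity of about 99.57%. With m = 28 the break-even is about 98.7%.

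**Clustered errors.** Let f vary between children as a beta distribution with mean 1%. At m = 84, P(at least one) is 28%, 19% and 12% for within-child correlation of 0.05, 0.10 and 0.20. Averaging the two-sequence formula over the same distributions gives 16%, 13% and 9%, so a higher threshold protects less when errors cluster.

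**Against the planned contrast.** The planned net gain is 0.15×102 ≈ 15 children. Sample size estimates puts asthma at 33%, which leaves 0.67×102 ≈ 68 children. If all 68 were wheeze-free and made 84 recordings, the expected false 'yes' count is 0.0805×68 ≈ 5 at 99.9%, 0.342×68 ≈ 23 at 99.5% and 0.566×68 ≈ 39 at 99%. At 99% with correlation 0.05 to 0.20 it is about 19 to 8.

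**Significance.** Children who are 'definite yes' at T1 are not taught home monitoring. If they all keep that label, discordance runs one way. Six conversions then give an exact two-sided McNemar p of 2×0.5⁶ = 0.031; five give 0.0625. Six is 7% of the 0.85×102 ≈ 87 monitored children. If all 87 were wheeze-free with independent errors, the chance of at least six false conversions is about 0.7 at 99.9% specificity and practically 1 at 99.5%. This is an upper bound: the children are enrolled with symptoms, and the plan's own cells allow 6.4% to lose the label.

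**The case against.** A reader might infer that even a very specific device would reach 30% from false readings alone. The documents do not support that. They give no specificity, 99.9% yields only 8%, and at 99% a within-child correlation of 0.05 or more takes the figure below 30%. An error that persists in one child, such as upper-airway noise, would also tend to stay positive after SABA and lead to 'possible'.

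Nor does the pilot supply the missing error rate. The Introduction reports that parents noted wheeze in 22 of 708 recordings, "but WheezeScan indicated wheeze was present in 140/708 (19.8%) of the recordings". That mixes true and false positives, and it counts single readings rather than positive-then-negative sequences.

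A reader might also infer that McNemar's test would be significant with no diagnostic gain. On the (yes/no) wording of the endpoint, a wheeze-free child with clean readings already counts as definite. A false move to 'yes' changes nothing, and an unresolved false positive lowers the count. The inference needs the asthma-'yes' reading, which the hypothesis and the sample size use.

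Finally, the rule may not be applied mechanically. The treating specialist classifies, response to inhaled corticosteroids enters at T3, and a supplement that is not shown gives further description. All this stands and tempers the size. None of the shown text requires replication or allows for the number of recordings.

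**Conclusion.** The point holds as a risk of unknown size. As written, one sequence is enough for 'definite yes' and nothing limits accumulation over recordings. False sequences could label between about 8% (99.9% specificity) and 57% (99%) of wheeze-free children who make 84 recordings, if errors are independent. Clustering, missed recordings or clinical judgement would lower this; recordings made on suspicion would raise it. A rise in asthma 'yes' of the planned size could therefore be partly or wholly a product of repeated testing, and the planned analysis could not tell. How far this touches the primary result depends on whether the endpoint is asthma 'yes' or any definite answer, on which the hypothesis, the endpoint and the sample size do not agree.

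**What to change.** 1. Keep the treating clinician's classification as the primary endpoint, and reconcile Aims and hypotheses, the Primary endpoint and Sample size estimates on whether 'yes' or 'yes/no' is counted.
2. Pre-specify sensitivity McNemar analyses of asthma 'yes' that count a T3 'definite yes' only with at least 1, 2 or 3 documented positive-then-negative sequences on separate days.
3. Report recordings per child, routine and on suspicion, and the 'yes' rate expected from false readings over a range of specificity and within-child correlation.
4. State in advance that the conclusion will be limited if the increase does not survive these analyses.
5. Reconcile the abstract with the T1 and T2 sections on how long, and in whom, home recording continues. Reconcile the T1 and T2 sections, which allow a repeated SABA step, with Outcomes and endpoints, which names a single one.

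The cost is analysis-plan wording and reporting; the recordings are already collected, and the article says the detailed plan is still to be written. The downside is that true cases with one captured episode drop out at the higher thresholds. Children labelled 'yes' at T2 may start inhaled corticosteroid, and their continued recording is not stated, so they may have less chance of a second sequence. That is why the thresholds belong in sensitivity analyses, shown beside the number of recordings, and not in the primary definition.

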### Endpoints

#### Primary

Proportion of children with a definite diagnosis (yes/no) of asthma from T3 to T1, based on the classification provided by the treating specialist clinician.

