## Aims and hypotheses

Our primary aim is to determine in preschool children (aged 0.5–6 years) suspected of asthma whether adding WheezeScan to routine clinical assessment (vs assessment without WheezeScan) improves the diagnosis of asthma. Our primary hypothesis is that using WheezeScan in preschool children suspected of asthma is associated with increased definitive asthma diagnoses in this age group.

Our secondary aims are to examine the effect of using WheezeScan on: (a) PROs and (b) healthcare costs. Our secondary hypothesis is that using WheezeScan in preschool children suspected of asthma is associated with improved QoL without incurring additional healthcare costs.

Additionally, we aim to evaluate the perceived usefulness of WheezeScan for parents/caregivers using a qualitative evaluation.

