**Figure 2 F2:**
[figure not shown]
Study flow of our cohort study. Dx, diagnosis; FeNO, fractional exhaled nitric oxide; ICS, inhaled corticosteroids; PC-QoL, Parent Cough-Specific Quality-of-Life^29^; PedQL, Paediatric Quality-of-Life Inventory V.4^28^; PROs, patient reported outcomes; wks, weeks.

**Table 1 T1:** Outline of study procedures

Assessment	Baseline (T1) At enrolment or prior to starting study	From baseline	
		2 weeks T2	6 weeks T3
	Window:	±4 days	±4 days
Screening for eligibility	✓		
Informed consent	✓		
Sociodemographic and medical history	✓		
Medical chart review	✓		
Clinical assessment	✓	✓ (optional)	✓ (optional)
Classify asthma (yes/possible/no)	✓ (primary specialist clinician)	✓ (primary specialist clinician)	✓ (primary and independent specialist clinicians)
PedsQL^28^	✓	✓	✓
PC-QoL^29^ (if chronic cough present)	✓	✓	✓
Health surveillance questions		✓	✓
Spirometry (if aged >4 years); pre-SABA and post-SABA where possible	✓	✓ (if seen)	✓ (if seen)
FeNO (if aged >4 years) once during study, if possible	✓	✓ (if seen)	✓ (if seen)
Analyse WheezeScan data		✓	✓
Parent WheezeScan utilisation question*			✓
NASSS-informed qualitative interviews		✓	or ✓
Collect results for full blood count, RAST, IgE (if available as part of clinical request)†	✓		or ✓
Contact parent—general health and WheezeScan questions about any problems encountered	Every week between T1 and T3		

* Parent utilisation question ‘The WheezeScan is useful in managing my child’s wheezing problem’ 5-point Likert (range from 1=strongly disagree to 5=strongly agree).

† Recorded for possible future studies.

FeNO, fractional exhaled nitric oxide; IgE, Immunoglobulin E; NASSS, non-adoption, abandonment, scale-up, spread and sustainability; PC-QoL, Parent Cough-Specific Quality-of-Life; PedsQL, Paediatric Quality-of-Life Inventory V.4; RAST, radioallergosorbent test; SABA, short-acting β2 agonist.

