#### Secondary

Concordance of the asthma classification between the treating and independent specialist clinicians.Agreement between the clinical and WheezeScan detection of wheeze.Difference in PROs between the timepoints (T3−T1, T3−T2); subanalysed in accordance with whether inhaled corticosteroids were used.Composite measure of the ‘usefulness of WheezeScan’. We will consider WheezeScan clinically useful if: (a) WheezeScan assisted in a definite diagnosis (yes/no) or (b) PRO outcomes are superior in the WheezeScan-based versus independent asthma classification groups and (c) did not incur (net) healthcare costs during the study period.Healthcare resource use among the various classified groups (primary horizon at T3).

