#### Analyses

For the primary aim we will compare the proportions using McNemar’s test.

For the secondary aims:

Concordance of asthma classification (definite yes, definite no, possible) between the treating clinician and the independent specialist will be undertaken using weighted Kappa. Likewise, concordance between clinician and WheezeScan detected wheeze will be undertaken using Cohen’s Kappa.Change in PROs scores will be presented as means and SD and assessed by paired t-tests (assuming normal distribution) and the proportions with scores above the minimal clinically important difference (MCID) for each PRO in each group defined at T3 compared with T1.Composite measure of ‘usefulness of WheezeScan’ will be described and presented as numbers and percentages.Healthcare resource use associated with respiratory healthcare will be costed using actual costs (when known) or market rates from the perspectives of the healthcare system provider and families for each pathway (figure 2). Uncertainty estimates will be generated using bootstrap resampling (10 000 replications).

We anticipate reporting the last two secondary aims in a separate paper, as there will be a delay in the healthcare resource use analysis.

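### The primary event is not defined consistently: the endpoint section reads as any definite label (yes or no), while the hypothesis and sample size concern asthma 'yes' only, and power is documented only for the latter

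*Protocol article*

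**What the plan says.** Table 1 of the protocol article records the classification at three levels, "Classify asthma (yes/possible/no". The section on outcomes and endpoints names the levels at T2 and T3 'definite yes', 'definite no' and 'possible', so the word 'definite' attaches to both the yes and the no label.

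Four places describe the primary comparison:

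- Endpoints, Primary: "Proportion of children with a definite diagnosis (yes/no) of asthma from T3 to T1", as classified by the treating specialist.
- Abstract, Methods and analysis: "the proportion of children with a definitive asthma diagnosis, compared with baseline".
- Aims and hypotheses: "using WheezeScan in preschool children suspected of asthma is associated with increased definitive asthma diagnoses in this age group".
- Sample size estimates: "conservative estimates of 15% being diagnosed with asthma at T1 and 30% at T3", with a paired correlation of 25%, 102 children and power above 80%.

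The phrase with yes/no in brackets returns in the composite secondary endpoint, where one criterion is that "WheezeScan assisted in a definite diagnosis (yes/no". The Analyses section adds only this: "For the primary aim we will compare the proportions using" McNemar's test. It does not say how three labels become the two categories that test needs.

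**The concern.** McNemar's test uses only the children whose binary status changes, so the choice of which labels count as the event is the definition of the endpoint. Two choices are in play: 'definite yes' or 'definite no' against 'possible', and 'definite yes' against the other two.

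On the first choice, the test can miss the effect the hypothesis names, because missed asthma found in a child first labelled 'definite no' leaves no trace. It can also mimic that effect, because ruling asthma out in a 'possible' child counts as a success with no asthma diagnosed. Both routes are open in the design. Children labelled 'possible' or 'definite no' at T1 take the device home and are reclassified, and 'definite no' at the later timepoints requires only that no wheeze was documented.

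**Working it through.** **1. What each change of label contributes.** 'Gain' and 'loss' are the two discordant cells of McNemar's table; 'none' is concordant.

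| T1 to T3 | Any definite vs 'possible' | 'Yes' vs the rest |
|---|---|---|
| possible to yes | gain | gain |
| no to yes | none | gain |
| possible to no | gain | none |
| no to possible | loss | none |
| yes to possible | loss | loss |
| yes to no | none | loss |

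The two tables agree only for moves between 'possible' and 'yes'. The net change in 'any definite' equals the net change in 'yes' plus the net change in 'no'.

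**2. The plan's own figure.** Inputs from Sample size estimates: p1 = 0.15, p2 = 0.30, correlation r = 0.25, n = 102. Two-sided alpha of 0.05 is my assumption, as none is stated beside the power.

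- p11 = p1·p2 + r·√(p1(1−p1)p2(1−p2)) = 0.045 + 0.25 × √0.026775 = 0.0859
- T1 only: 0.15 − 0.0859 = 0.0641. T3 only: 0.30 − 0.0859 = 0.2141
- Sum s = 0.2782; difference d = 0.15
- Power = Φ[(d√n − 1.96√s) / √(s − d²)] = Φ[(1.515 − 1.034) / 0.506] = Φ(0.952) = 82.9%

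The same approximation needs n = 95 for 80%. Enumerating the discordant count at n = 102 gives 85.5% for the uncorrected test, 79.2% with continuity correction and 79.3% for the exact conditional test. The stated figure therefore reproduces on the usual normal approximation, for 'yes' versus the rest.

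**3. The same formula for any definite label.** The document gives no 'definite no' rates, so those below are assumptions. 'Yes' goes from 15% to 30% throughout, with r = 0.25 and n = 102.

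| 'No' at T1, T3 | Any definite at T1, T3 | Power | n for 80% |
|---|---|---|---|
| 10%, 10% | 25%, 40% | 74% | 118 |
| 20%, 20% | 35%, 50% | 70% | 131 |
| 30%, 30% | 45%, 60% | 69% | 134 |
| 30%, 20% | 45%, 50% | 13% | 1177 |
| 30%, 15% | 45%, 45% | alpha only | none |
| 20%, 30% | 35%, 60% | 98% | 50 |

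In the fifth row the proportion with asthma diagnosed doubles exactly as planned, yet the expected McNemar difference is zero. The correlation matters too: 35% to 50% gives about 79% at r = 0.4 and 85% at r = 0.5.

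**The case against.** The bracketed yes/no may be no more than the coding of a binary variable, definite asthma or not. The endpoint would then match the abstract, the hypothesis and the sample size, and the power would be its own. This is possible for the endpoint sentence taken alone. The labels 'definite yes' and 'definite no', and the same phrase in the composite endpoint, where a definite answer in either direction seems meant, count against it. What stands is that the wider reading is the more natural one, not a certain one.

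Any definite label is also a defensible endpoint. The primary aim is to improve the diagnosis of asthma, and ruling it out can serve that aim. This stands, and it is why the remedy is to align the text rather than to declare one endpoint correct.

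A reader might infer that the study is underpowered, at about 70%. The document does not support that: the figure holds only if the 'definite no' share stays constant and the correlation stays at 0.25. A device that resolves 'possible' labels could raise that share and take power well above 80%.

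A reader might also infer that the endpoint hides corrected over-diagnosis, since 'definite yes' to 'definite no' is concordant. That is true of the table but weak in this design. Under the baseline procedures, children labelled 'definite yes' at T1 receive routine treatment, are not seen again until T3 and are not among those taught home use of the device.

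Finally, a reader might suspect that the definition would be picked after seeing results. The article promises a detailed analysis plan before the analyses and points to a supplement on outcomes; neither is at hand. A data-driven choice is a risk left open, not something the text states. Those documents may settle the definition, but they would not remove the conflict between the article's own sections.

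**Conclusion.** The concern holds as an inconsistency in the definition of the primary event. The endpoint section most naturally means any definite label, while the abstract, hypothesis and sample size mean 'yes' only. The difference is material: on the wider reading, the test ignores 'definite no' to 'definite yes' and credits 'possible' to 'definite no'.

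The power calculation itself is sound. It gives about 83% for 'yes' versus the rest, given the article's rates and correlation and an assumed two-sided alpha of 0.05. For any definite label, power is not established. It may be lower or higher than 80%, and the scenarios shown run from no more than alpha to 98%, depending on 'definite no' rates that I assumed.

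**What to change.** Before the data are analysed, state in one sentence which labels are the event at T1 and T3. Use that wording in the abstract, the hypothesis, the primary endpoint and the sample size.

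- **If 'yes' is meant:** define the event as 'definite yes' versus 'possible' or 'definite no'. This matches the hypothesis and keeps the power statement valid. Any definite label can become a secondary endpoint.
- **If any definite label is meant, or is what was registered:** keep it, reword the hypothesis to cover definite diagnoses in both directions, and restate the power with explicit assumptions for 'definite no' at T1 and T3.

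In either case, report the full 3x3 table of T1 by T3 labels so that moves between 'no' and 'yes' are visible.

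No new data are needed. The cost is a documented clarification or amendment of the primary endpoint while recruitment, open since 1 February 2024, is under way. If the chosen event differs from the registered one, that is a change of primary outcome during the study and should be reported as such.

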#### At baseline (timepoint 1 (T1))

We are collecting study PROs (Paediatric Quality-of-Life Inventory V.4 (PedsQL)^28^ (in all children) and Parent Cough-Specific Quality-of-Life (PC-QoL)^29^ (if chronic cough present) questionnaires, as done previously^23^ and sociodemographic and clinical data (eg, age, sex, family/household size, personal and family history of atopy, ethnicity (eg, First Nations), medications used, tobacco or e-cigarette exposure and immunisation history) from the parents/caregivers, medical notes and the Australian Immunisation Register.

As per routine practice, children are assessed clinically by a paediatric specialist, most of whom are respiratory specialists. Those who are classified as ‘definite yes’ receive routine clinical treatment and are not seen again until timepoint 3 (T3). All children have the WheezeScan applied and if wheeze is present, the child is given 400 µg (four puffs) of inhaled SABA (using a spacer±mask), the standard dose to define presence/absence of a bronchodilator response.^11^ After 10 min, the WheezeScan is used again to determine whether wheeze is still present and the results recorded. Whenever possible, fractional exhaled nitric oxide (FeNO) is measured, but the clinician is blinded to the result.

A member of the research team then teaches the parents/caregivers of those classified as ‘possible’ and ‘definite no’ how to use the WheezeScan and the e-diary, both of which are to be used routinely two times per day for the next 2 weeks and when wheeze is suspected by the parents/caregivers (eg, postphysical activity). The parents/caregivers are asked to give 400 µg of inhaled SABA (using a spacer±mask) if wheeze is detected and to then reapply WheezeScan 10 min later to determine and record whether RAO is present. If wheeze is still present, the parents are asked to give a further 400 µg of inhaled SABA (as above), and then to reapply WheezeScan again 10 min later, and record whether RAO is present.

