#### Final visit (timepoint 3 (T3))

6 weeks post-T1, the children are then again reclassified using WheezeScan data and response to inhaled corticosteroids, the latter if used following T2 (Dx-T3). Also, at T3, PROs and economic data from all study participants are collected.

At the end of the study, a second independent respiratory specialist reviews clinical data, including available FeNO results and WheezeScan data, from all participating children and based on this information classifies the asthma diagnosis in the child (labelled as the independent classification [i-]). The independent person is blinded to the treating clinician’s assessment.

In addition, parents/caregivers of those who used the WheezeScan are also asked to give feedback on the usefulness of the device, using a Likert scale question. The question, framed with advice from our consumer’s group, is as follows: ‘The WheezeScan is useful in managing my child’s wheezing problems?’ The Likert scale ranges from 1 (strongly disagree) to 5 (strongly agree).

Study exit criteria are: consent withdrawn or intolerance of SABA or inhaled corticosteroids (as determined by study site doctors or treating clinicians).

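### Both primary asthma labels come from the treating clinician role, with no masking of the T3 label to the T1 label, and the blinded T3 read cannot isolate upgrading

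*Protocol article*

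**What the plan says.** **Who assigns the primary label.** The primary endpoint compares T3 with T1, "based on the classification provided by the treating specialist clinician" (Endpoints, Primary). Table 1 has the primary specialist clinician classify at T1 and T2, and at T3 lists "primary and independent specialist clinicians". Under Analyses: "For the primary aim we will compare the proportions using McNemar’s test".

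**What that clinician may use.** The T1 label rests on clinical parameters. For T2 and T3, Outcomes and endpoints defines 'definite yes' as "presence of RAO defined by disappearance of wheeze using WheezeScan after 400 µg of inhaled SABA", 'definite no' as no documented wheeze, and 'possible' as wheeze without a clear response or anything that fits neither category. The Final visit section says that at T3 "the children are then again reclassified using WheezeScan data and response to inhaled corticosteroids", the latter where they were used. The only masking described for the treating clinician is at baseline: "fractional exhaled nitric oxide (FeNO) is measured, but the clinician is blinded to the result".

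**The independent read.** A second specialist classifies every child at the end of the study, and "The independent person is blinded to the treating clinician’s assessment". This reader has separate categories. 'i-Asthma' is "resolution of symptoms with treatment using WheezeScan data supported by FeNO >25ppb (if available"), 'i-no' is absence of a treatment effect, and 'i-possible' is the remainder. The read enters the weighted kappa and, as a comparator grouping, the composite usefulness measure (Endpoints, Secondary).

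**The concern.** A before-after comparison with no control group depends on the two labels being assigned in a way that does not favour movement in one direction. Here the role that gave the first label also gives the second, knowing that the device is under evaluation and, as far as the article says, with the first label in view. If that leads to some children moving from 'possible' to 'definite yes' beyond what the device readings support, the primary test counts those moves as the hypothesised effect.

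A written rule for T3 should limit this, but the article loosens it in three places:

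- Corticosteroid response may enter the T3 label although the rule does not mention it.
- 'Possible' is a catch-all category.
- The rule names one 400 µg SABA dose, while the baseline and T2 sections allow the SABA and WheezeScan step to be repeated once.

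The natural safeguard, a blinded second reader, is planned but is not set up to test this.

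**Working it through.** **1. The plan's own figure.** Inputs from Sample size estimates: 15% at T1, 30% at T3, correlation 0.25, power above 80%, N = 102. Alpha is not stated; two-sided 0.05 is assumed.

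- Both positive: p11 = 0.15×0.30 + 0.25×√(0.15×0.85×0.30×0.70) = 0.0859.
- Discordant cells: 0.30 − 0.0859 = 0.2141 (up) and 0.15 − 0.0859 = 0.0641 (down). Sum s = 0.2782, difference d = 0.15.
- n = [1.96√s + 0.8416√(s − d²)]²/d² = 94.6. With the continuity correction, n = 101.2, rounded up to 102.

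The stated 102 reproduces, so the sample-size arithmetic is not in question. On these inputs about 0.0641×102 = 6.5 children move down.

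**2. How many upgrades would give a significant result?** Assume no true change and c children moving each way. Take c = 6, close to the planned downward cell, and c = 10 as a wider case. Both values are assumptions. Add u discretionary upgrades, so b = c + u. The uncorrected statistic is (b − c)²/(b + c). The exact p-value is twice the binomial tail with probability 0.5. The article does not name the variant, so both are shown.

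| Up v down | Upgrades u | Uncorrected p | Exact p |
|---|---|---|---|
| 14 v 6 | 8 | 0.074 | 0.115 |
| 15 v 6 | 9 | 0.0495 | 0.078 |
| 16 v 6 | 10 | 0.033 | 0.052 |
| 17 v 6 | 11 | 0.022 | 0.035 |
| 20 v 10 | 10 | 0.068 | 0.099 |
| 21 v 10 | 11 | 0.048 | 0.071 |
| 22 v 10 | 12 | 0.034 | 0.0501 |
| 23 v 10 | 13 | 0.024 | 0.035 |

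For example, (15 − 6)²/21 = 3.857 and (21 − 10)²/31 = 3.903. The uncorrected test needs 9 to 11 upgrades (9/102 = 8.8%, 11/102 = 10.8%). The exact test needs 11 to 13 (10.8% to 12.7%). The design difference is 0.15×102, about 15 children.

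**3. The same question as an error rate.** Assume each discordant cell is 5% to 10% with no true change. If an extra 5% of children are moved to 'yes', the uncorrected test rejects in 18% to 25% of studies and the exact test in 12% to 18%. At an extra 10% the figures are 47% to 65% and 38% to 55%.

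**4. Could the independent read reveal it?**

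| | Treating clinician, T3 | Independent reader |
|---|---|---|
| Yes | Device wheeze disappears after SABA | Symptoms resolve with treatment, FeNO support if available |
| No | No wheeze documented | No effect of treatment |
| T1 counterpart | Yes, on clinical parameters | None |

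A child with no wheeze and no treatment is 'definite no' in the first column and has no treatment effect to judge in the second. Disagreement in the kappa table can therefore come from the rater or from the definition, and the table cannot say which. With no independent T1 label, the read cannot be put into a paired test either.

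**The case against.** **Seeing the device data is the intervention.** The aim is whether adding WheezeScan changes diagnosis, so the clinician cannot be masked to it. This stands, and nothing here asks for it. Masking the application of the T3 rule to the T1 label is a different matter; it is possible and is not described.

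**A sensitivity analysis belongs in the SAP.** The article promises a SAP, including adjustment for potential biases, and it is not shown. The absence of that analysis from the article is therefore not the fault. What the article itself fixes is the rater, two differing accounts of what enters the T3 label, and an independent read whose categories do not match.

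**The T3 rule limits discretion.** It does: 'definite yes' requires wheeze to disappear on the device. The room left is the corticosteroid clause, the catch-all category, and unresolved repeat-dose and mixed episodes.

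**Stronger readings that the article does not support.**

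- A reader might infer that the same individual gives both labels. Table 1 names a role only.
- A reader might infer that the independent read serves the kappa alone. It also enters the composite measure.
- A reader might infer that no planned analysis could show any sign of upgrading. An excess of treating-clinician 'yes' against 'i-possible' or 'i-no' would be a signal, though one confounded with definition.
- A reader might infer that the T3 rule can be run mechanically on all 102 children. Under the baseline section, only children labelled 'possible' or 'definite no' at T1 are taught home WheezeScan and the e-diary. At the planned 15%, about 15 children (0.15×102 = 15.3) have no described home records.

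**Conclusion.** The concern holds in this form: both primary labels belong to the treating clinician role, no masking of the T3 label to the T1 label is described, the T3 inputs differ between two sections, and the blinded read cannot isolate upgrading. The limitations section concedes risk of bias from the non-randomised design but does not address assessor bias.

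Its size is illustrative. With 6 or 10 children moving each way and no true change, 9 to 11 upgrades suffice with the uncorrected test and 11 to 13 with the exact test. No figure in the article says that upgrading happens at that rate, or at all; the point is that the result would be open to it. The counts treat the label as 'definite yes' against the rest, in line with the sample-size section. This is worth fixing before the SAP is final, but it does not call for a different primary endpoint.

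**What to change.** Keep the treating clinician's label as primary, and make these changes:

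1. **Reconcile the T3 inputs.** State whether corticosteroid response enters the T3 label, and reconcile the Final visit section with Outcomes and endpoints. Reconcile likewise the single 400 µg in the rule with the repeat step in the baseline and T2 sections. Which version applies is for the investigators.
2. **Prespecify a sensitivity analysis.** For children given home WheezeScan (T1 'possible' or 'definite no'), derive the T3 label from the WheezeScan and e-diary records by the reconciled rule, without sight of the T1 label. Fix the handling of repeat SABA and of mixed episodes beforehand.
3. **Treat T1 'definite yes' children separately.** Keep the clinician's T3 label for them. Scoring absent home records as no documented wheeze would create false yes-to-no moves in the cells that McNemar's test uses.
4. **Repeat McNemar's test** on all children with these labels, and report the cross-table of clinician label against rule-derived label for those with home records.

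The cost is agreement on the rule, some programming and one table, on data already being collected and with no further assessor. The analysis may give a second, less favourable estimate. It does not remove the change from a clinical criterion at T1 to a device criterion at T3, which should be stated as a limitation.
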